**Aim 2: Determine the patient-reported acceptability of TLT in the ED.**

Hypothesis: The patients and surrogates undergoing TLT conversations will feel heard and understood about their end-of-life care wishes (primary acceptability outcome).

Descriptive statistics will be used for baseline characteristics of the study sample. We will compare patient demographics between study arms to assess randomization using two sample t-test or Wilcoxon rank sum test for continuous variables and chi-square for categorical variables. Within arms, we will use a one-sample binomial exact test of proportions for categorical outcomes (e.g., EHR documentation), and Wilcoxon signed ranks test for ordinal outcomes (e.g., Heard and Understood survey). A significance level, alpha, is set to 0.05. We will conduct a secondary analysis using linear mixed models at baseline and one month to include all non-missing data. The EHR-based outcome will be assessed using an EHR review. We will publish our findings regardless of the results and will follow the CONSORT guidelines for reporting RCT.^43^

**Sample Size:** No previous two-arm trial of TLT has been conducted; thus, the effect size remains unknown. Given the primary purpose of conducting a RCT is to demonstrate the feasibility of conducting a randomized design study, no gold standard for sample size calculations exists. However, prior literature suggest that 15 to 20 participants per group are required to ensure scientific validity of the pilot study results.^44^ Therefore, the present study will include a total of 32 participants with 16 participants per group. In addition, the results of this pilot study will provide information on the difference between groups and standard deviation necessary for sample size calculation during the future full-scale study.

1. **MONITORING AND QUALITY ASSURANCE**

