Aim 1: Determine the clinician-reported feasibility of conducting a clinician-level, randomized controlled trial of TLT compared to usual care in the ED.

Hypothesis: TLT is feasible to conduct a clinical-level randomized study in the ED.

Aim 2: Determine the patient-reported acceptability of TLT in the ED.

Hypothesis: The patients or surrogates (if patients are unable to consent) randomized to TLT will feel more heard and understood about their end-of-life care wishes (primary outcome).

1. **GENERAL DESCRIPTION OF THE STUDY DESIGN**

Overview

To demonstrate the feasibility (Aim 1) and acceptability (Aim 2) of TLT, we will conduct a parallel group, clinician-level, pilot randomized clinical trial among 40 emergency clinicians (~20 in TLT and ~20 in usual care) in the ED.

Randomization: Using REDCap’s integrated randomization module,^24^ we will conduct clinician-level randomization using random blocks of four to ensure that emergency clinicians are evenly distributed one-to-one between intervention and control arms.

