Outcome Assessments: We will collect the following variables during and after the TLT conversations (Table 2).

For Aim 1 Feasibility, we will collect all outcomes from the intervention arm, and EHR outcome from both intervention and control arms.

For Aim 2 Patient-Reported Acceptability, we will collect all outcomes from both the intervention and control arms.

*For clarity, we placed * on outcomes only collected from the intervention arm.*

| **Table 2. Outcomes and Assessment Timing** | | |
| --- | --- | --- |
| **Aim 1: Feasibility (* indicates outcomes collected only from the intervention arm)** | | |
| **Outcomes** | **Descriptions** | **Timing** |
| Time to complete the TLT conversation (primary outcome)* | With direct observation, the study team will record how long it takes to complete the TLT conversation by the intervenist ED clinician. | At the time of TLT conversation |
| Intervention fidelity* | With direct observation, the study team will record the completion of TLT components using an intervention fidelity checklist. | At the time of TLT conversation |
| Clinician-reported feasibility* | The study team will ask the interventionist emergency clinician to complete two 5-point Likert scale questions (i.e., “How feasible was it to conduct the TLT conversation with your patient?” and “How likely would you recommend the TLT conversation for your colleagues?” “Not at all (1)” to “Completely (5)”). | Immediately after the TLT conversation |
| Recruitment* | The percent that agree to conduct TLT conversations | At enrollment |
| Clinician-reported satisfaction* | The study team will ask the interventionist emergency clinician to complete 5-point Likert scale questions (i.e., “How satisfied are you with the conversation? “Not at all (1)” to “Completely (5)”). | Immediately after the TLT conversation |
| EHR documentation by inpatient clinicians (i.e., intensivists) | Review EHR for new documentation of reference to TLT, serious illness conversation, change in code status, or advance directive forms by inpatient clinicians. | After 24 hours, 48 hours, and 1 week |
| **Am 2: Patient-Reported Acceptability (* indicates outcomes collected only from the intervention arm)** | | |
| **Outcomes** | **Descriptions** | **Timing** |

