| Patient-reported acceptability of TLT conversation (primary outcome)* | A 5-point Likert scale (i.e., “How acceptable was it for your doctor to talk to you about your expectations for ICU care?” and “How likely would you recommend this conversation for other patients like you?” “Not at all (1)” to “Completely (5)”). | Immediately after the TLT conversation |
| Heard and understood | A National Quality Forum endorsed, validated measure for palliative care modified to fit the context of serious illness conversations (“How well they feel heard and understood by your emergency department clinician about medical care they would want if they were to get sicker?” a 5-point Likert scale “Not at all (1)” to “Completely (5)”).^39^ | Immediately after the TLT conversation |
| Patient-reported end-of-life quality of communication | A validated, quality of end-of-life communication survey (4 items selected a priori, a 10-point Likert scale “Worst you can imagine (0)” to “Best you can imagine (10)”).^40^ | Immediately after the TLT conversation |
| Decisional regret scale | A validated survey that measures “distress or remorse after a [health care] decision” (5 items, 5-point Likert scale “Strongly agree (1)” to “Strongly disagree (5)”).^41^ | After 24 hours, 48 hours, and 1 week |
| Clinical outcomes abstracted from EHR | Number of days to the first family meeting in intensive care unit (ICU), ICU length of stay (LOS), hospital LOS, # family meetings, ICU procedures (e.g., CPR, pressors, etc.), ICU mortality, hospital disposition, hospice utilization. | After discharge or upon patient death |

A research assistant blinded to treatment allocation will perform all follow-up assessments. Our team will extract data from the EHR using a standardized approach.^42^

Study Termination:

We will follow the participating clinicians for up to one year to accrue an adequate number of patients they admit to the intensive care unit. Given that an emergency clinician may encounter ~3 to 10 seriously ill older adults being admitted to the intensive care unit per month, we estimate that it would take approximately one year to accrue ~10 patient/interventionist ED clinician who might meet the inclusion/exclusion criteria for Aim 2. The follow-up assessments of the patients will terminate when/if the participants die or are discharged from the hospital.

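### Clinicians are randomised, but the tests named for patient data assume independent patients, and the pilot promises no between-clinician variance for the full trial

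*Protocol*

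**What the plan says.** **Unit of randomisation.** Under General Description of the Study Design the Protocol states: "we will conduct clinician-level randomization using random blocks of four to ensure that emergency clinicians are evenly distributed one-to-one". The same section describes a "pilot randomized clinical trial among 40 emergency clinicians (~20 in TLT and ~20 in usual care) in the ED".

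**Patients per clinician.** Under Study Termination the forecast is: "we estimate that it would take approximately one year to accrue ~10 patient/interventionist ED clinician". It refers to patients who might prove eligible, and to the intervention arm.

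**Arms.** For Aim 2, Outcome Assessments says "we will collect all outcomes from both the intervention and control arms", apart from the items starred in Table 2. The heard-and-understood item is not starred.

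**Tests.** Statistical Analysis, Aim 2, covers patient demographics with the sentence "We will compare patient demographics between study arms to assess randomization using two sample t-test or Wilcoxon rank sum test for continuous variables" and adds chi-square for categorical variables. Outcomes are tested within each arm, by a one-sample exact binomial test (categorical) or a Wilcoxon signed-rank test (ordinal), at alpha 0.05. A secondary linear mixed model over two time points is also named, without a clinician effect.

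**Use of the pilot.** The Sample Size paragraph sets 32 participants, 16 per group, without saying whether they are clinicians or patients. It adds that "the results of this pilot study will provide information on the difference between groups and standard deviation necessary for sample size calculation". Clustering, an ICC and a design effect are not mentioned anywhere.

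**The concern.** When clinicians are randomised and each treats several patients, patients of one clinician tend to resemble each other. That is plausible here above all for the heard-and-understood item, which asks about the patient's own emergency clinician. A test that counts each patient as a separate piece of information then uses a standard error that is too small, and its p-value is too optimistic.

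Two further things are at stake. First, a stated use of the pilot is to supply inputs for sizing a full trial. If that trial also randomises clinicians, the difference and SD are not enough. Second, patients were not randomised and enter after clinicians have been allocated. A patient-level significance test therefore cannot check the randomisation, and it carries the same clustering error.

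**Working it through.** **Step 1: the plan's own figure.** 2 × 16 = 32, and 16 lies within the cited range of 15 to 20 per group. There is no power calculation to reproduce. The 32 does not agree with the 40 clinicians in the design section.

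**Step 2: inputs.**
- Clinicians per arm: about 20 (design section), or 16 if the 32 are clinicians.
- Patients per clinician, m: about 10 as a forecast (Study Termination). Values 1 and 5 are added because the number enrolled may be lower.
- Alpha: 0.05 (Statistical Analysis), taken as two-sided because the sidedness is not stated.
- ICC: not in the documents. Assumed 0.05 and 0.10.

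**Step 3: true error of a nominal 5% test that ignores clustering.** Design effect DE = 1 + (m − 1) × ICC. True error = 2 × [1 − Φ(1.96/√DE)].

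Example with m = 10 and ICC 0.05: DE = 1 + 9 × 0.05 = 1.45, √DE = 1.204, 1.96/1.204 = 1.628, and 2 × [1 − Φ(1.628)] = 0.104.

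| m | ICC | DE | True SE / naive SE | True error |
|---|---|---|---|---|
| 1 | any | 1.00 | 1.00 | 5.0% |
| 5 | 0.05 | 1.20 | 1.10 | 7.4% |
| 5 | 0.10 | 1.40 | 1.18 | 9.8% |
| 10 | 0.05 | 1.45 | 1.20 | 10.4% |
| 10 | 0.10 | 1.90 | 1.38 | 15.5% |

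**Step 4: check by simulation (m = 10, 20 clinicians per arm, no true effect).**
- A patient-level two-sample t-test rejected in 5.2%, 10.5% and 15.4% of 10,000 trials at ICC 0, 0.05 and 0.10.
- A t-test on clinician means rejected in 5.0%, 5.0% and 4.8%.
- With 16 clinicians per arm, the patient-level test rejected in 10.7% at ICC 0.05.
- The one-sample exact binomial test, which the plan names for outcomes, rejected in 3.8%, 8.9% and 13.6% of 20,000 runs at ICC 0, 0.05 and 0.10. A null of 0.5 was assumed because the Protocol gives none.

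**Step 5: consequence for the full trial.** If it is sized for 80% power as though patients were independent, actual power = Φ[(1.96 + 0.8416)/√DE − 1.96]. At m = 10:
- ICC 0.05: 2.8016/1.204 − 1.96 = 0.37, power about 64%.
- ICC 0.10: 2.8016/1.378 − 1.96 = 0.07, power about 53%.

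**Step 6: what the 32 does to this.** If the 32 are patients spread over 40 clinicians, 32/40 = 0.8, so m is about 1, DE is about 1 and the inflation disappears. If they are clinicians with about 10 patients each, the results above are almost unchanged.

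**The case against.** **The between-arm tests are for demographics only.** This stands. The sentence naming the t-test and rank-sum test does not cover outcomes, and no between-arm outcome test is named. A reader might infer that the trial's main arm comparison runs at a 10% to 15% error rate. The documents do not support that, because no such comparison is specified. The within-arm outcome tests also assume independence, but they have no stated null, so their error rate cannot be fixed exactly.

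**Ten patients per clinician is a forecast.** This stands too. It counts possibly eligible patients of interventionist clinicians, before the daytime recruitment window and consent. That is why the results are shown for m from 1 to 10.

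**A mixed model is named.** It is wrong to say that every named analysis ignores clustering, and the random effects may be set out in an SAP that is not shown. But this model is secondary, its stated aim is to use all available data over time, and it does not change the tests the Protocol itself chooses.

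**No confidence intervals are named, and an ICC could still be estimated.** Both are correct. A reader might infer that the pilot cannot yield an ICC. In fact clinician-linked data would allow one if clinicians contribute several patients; the plan just does not promise it. The power loss would arise only if the next trial's designers ignored clustering.

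**Comparing patients between arms has a use.** It can reveal selective recruitment after allocation. A descriptive comparison serves that purpose without claiming to test the randomisation.

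**Conclusion.** The point holds. The tests the Protocol states for patient data do not fit its own unit of randomisation, and the quantity that a clinician-randomised full trial would need is not among the promised results.

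The size is conditional. It is nil at one patient per clinician, moderate at five and two to three times the nominal error at ten, for an assumed ICC of 0.05 to 0.10. Nothing in the documents fixes the ICC, and the undefined 32 participants leave m open.

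A reader might go further and conclude that the feasibility findings are unsound. They are not touched: the Aim 1 criteria are descriptive thresholds (median conversation time, share of components completed, share of clinicians rating the conversation feasible) and do not rest on these p-values.

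**What to change.** In Statistical Analysis, Aim 2, and Sample Size:

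1. State that patient-level outcomes, including any between-arm comparison, are analysed with a clinician random intercept and a small-sample correction, or on clinician-level means.
2. Add the ICC, with its confidence interval, as a pilot result beside the SD.
3. State whether the 32 participants are clinicians or patients, and reconcile this with the 40 clinicians and the forecast of about 10 patients per clinician. Settle this early, because with about one patient per clinician an ICC is barely estimable.
4. Remove patient-level significance tests as a check of randomisation, and describe patient and clinician characteristics by arm instead.

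The cost is text only, with no added patients or procedures. Standard errors become about 20% wider at ICC 0.05 and 38% wider at ICC 0.10 when m = 10. The ICC itself will be imprecise with 32 to 40 clinicians and should be reported as such.

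### The Aim 2 hypothesis compares arms on Heard and Understood, but the plan names only a within-arm test for it and specifies no between-arm outcome analysis

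*Protocol*

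**What the plan says.** **Hypothesis.** Under Specific Aims and Objectives, Aim 2 predicts that patients or surrogates "randomized to TLT will feel more heard and understood about their end-of-life care wishes (primary outcome"). The Aim 2 part of Statistical Analysis restates this without a comparator: "The patients and surrogates undergoing TLT conversations will feel heard and understood about their end-of-life care wishes (primary acceptability outcome").

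**Collection.** Outcome Assessments (Study Procedures) says that Aim 2 outcomes come from both arms and that an asterisk marks intervention-only items. In Table 2, Heard and Understood has no asterisk. Its single assessment time is "Immediately after the TLT conversation". The item that Table 2 labels primary for Aim 2 is a different one, acceptability, and it is asterisked.

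**Analysis.** The Aim 2 statistics paragraph says "Within arms, we will use a one-sample binomial exact test of proportions for categorical outcomes (e.g., EHR documentation), and Wilcoxon signed ranks test". The latter test is assigned to ordinal measures, and Heard and Understood is the example given. The paragraph names between-arm tests only for baseline balance: "We will compare patient demographics between study arms to assess randomization using two sample t-test or Wilcoxon rank sum test", with chi-square for categorical variables. It adds: "We will conduct a secondary analysis using linear mixed models at baseline and one month to include all non-missing data".

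**Purpose.** The Sample Size paragraph sets 16 participants per group and says that "the results of this pilot study will provide information on the difference between groups and standard deviation necessary for sample size calculation" in a later trial.

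**The concern.** A hypothesis that one randomised group will feel more heard than the other is answered by comparing the groups. The plan gives this outcome, by name, a test that looks at each arm alone. Such a test can show that scores in an arm lie away from some chosen value. It cannot show that TLT differs from usual care.

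Two things are at stake. The declared primary hypothesis of Aim 2 has no analysis that could support or refute it. And the quantity the pilot is meant to hand to the full trial, a group difference, has no specified estimate or interval. There is also a risk in reporting: with two within-arm p-values in hand, it is easy to read significance in one arm only as evidence of a difference.

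**Working it through.** **Step 1. Hypothesis, data and analysis side by side, for Heard and Understood.**

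| Element | Place in protocol | Content |
|---|---|---|
| Hypothesis | Specific Aims, Aim 2 | Comparative, labelled primary |
| Hypothesis restated | Statistical Analysis, Aim 2 | No comparator, labelled primary |
| Arms measured | Outcome Assessments and Table 2 | Both |
| Times measured | Table 2 | One |
| Test named | Statistical Analysis, Aim 2 | Signed ranks, within arm |
| Between-arm tests named | Statistical Analysis, Aim 2 | Demographics only |

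**Step 2. Can the named test be run?** A signed-ranks test needs either paired values or a reference value. Table 2 gives one value per respondent, so there is no pair. No reference value is stated. For this item the test is undefined as written.

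**Step 3. Does the mixed model fill the gap?** It names neither an outcome nor an arm term. It is set at baseline and one month. Heard and Understood has neither time point, and Table 2 lists no one-month assessment for any outcome.

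**Step 4. What within-arm significance would convey (illustration).** Suppose the two arms are identical and each independent within-arm test has power p against some reference value. The p values are assumed.

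- P(exactly one arm significant) = 2p(1−p). At p = 0.5: 2 × 0.5 × 0.5 = 0.50. At p = 0.8: 2 × 0.8 × 0.2 = 0.32. The comparable two-sided between-arm error is 5%.
- P(only TLT significant) = p(1−p). This gives 0.25 and 0.16. The comparable one-directional error is about 2.5%.

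A simulation agrees (4,000 runs, 16 independent patients per arm, same assumed response distribution in both arms, assumed reference of 3):

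| Shared mean | Each arm significant | Exactly one arm significant | Between-arm rank-sum rejects |
|---|---|---|---|
| 3.65 | about 55% | about 49% | about 4.7% |
| 4.0 | about 82–83% | about 29% | about 4.7% |

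**Step 5. What a between-arm estimate would deliver.** The stated size reproduces as arithmetic: 16 × 2 = 32, and 16 lies within the cited 15 to 20 per group. It is not a power calculation. Taking a two-sided 0.05 level (sidedness is not stated) and ignoring clustering:

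- 95% CI half-width = 1.96 × √(2/16) = 0.69 SD.
- Difference detectable with 80% power = (1.96 + 0.84) × √(2/16) = 0.99 SD.
- With the roughly 20 per arm of the study design section, these become 0.62 SD and 0.89 SD.

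**The case against.** **The statistics section's own hypothesis is not comparative.** Without the word more, a within-arm analysis fits it better. That is so, and it makes the root problem an unreconciled hypothesis and primary outcome. It does not rescue the plan: the Specific Aims version remains, and the signed-ranks test still has no pair or reference value.

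**A reader might infer that the randomised comparison is used for no outcome.** The text does not go that far. The secondary mixed model could carry an arm term; none is stated. What stands is that no between-arm outcome analysis is specified.

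**A reader might also infer that the full trial will get no group difference at all.** Simple summaries by arm would yield a raw difference and an SD, so this is too strong. What is missing is a specified estimate with its uncertainty.

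**The 50% and 32% figures could be read as this trial's error rate.** They are not. The protocol nowhere says that it will compare significance across arms, and the powers are assumed.

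**The missing null proportion and reference value are details often left to a statistical analysis plan.** Alone they would not be a finding. They matter here because the protocol fixes a test that does not answer its own question.

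**Signed ranks is not undefined for everything.** Decisional regret is measured at 24 hours, 48 hours and 1 week, so paired change exists there. The objection to the test on that ground is confined to Heard and Understood.

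**This is a feasibility pilot.** A formal test is not essential, and with 16 per arm it would be weak. That bears on severity and favours estimation.

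**Conclusion.** The point holds in this form. The protocol states a comparative primary hypothesis, collects the outcome in both arms, and then assigns it by name a within-arm test that cannot be run on a once-measured item without a reference value and would not address the hypothesis if it could. Because the analysis is stated, not left open, this is a mismatch within the document and not merely an omission that an unseen statistical analysis plan may cover.

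Its size is one of validity: as written, the Specific Aims hypothesis cannot be tested, and no between-group estimate with an interval is specified. The probabilities in the working illustrate why within-arm significance is not a substitute; they depend on assumed power and identical, independent arms.

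Severity is should-fix. The Aim 1 feasibility thresholds, which carry the pilot's main purpose, are untouched.

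**What to change.** 1. **Reconcile the hypothesis and the primary outcome** across Specific Aims, Table 2 and Statistical Analysis: comparative or not, and Heard and Understood or acceptability.
2. **Replace the within-arm tests for the two-arm outcomes** with a between-arm estimate and 95% CI by the clinician's randomised arm, allowing for patients clustered within clinicians. Use a cluster-robust interval or a clinician random intercept, as the number of patients per clinician permits. This needs the sample size settled: 32 participants, if patients, spread over 40 clinicians average 32/40 = 0.8 each, too few for a random intercept, whereas the roughly 10 per interventionist clinician under Study Termination would support one.
3. **For decisional regret,** include time and a patient-level effect, since it is assessed three times.
4. **Drop the signed-ranks test for Heard and Understood.** Keep one-arm exact intervals for intervention-only items.
5. **Reconcile control-arm surveying.** Outcome Assessments promises both arms. But the Aim 2 paragraph of the study design section describes only record review for control patients, and Subject Selection and Subject Enrollment describe approach and consent only after a TLT conversation. The survey time in Table 2 likewise has no anchor in the control arm. State how and when control respondents are approached.

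**Cost.** Items 1 to 4 take a few sentences. Item 5 is a procedural clarification, and may mean extra control-arm consent and survey work if only the narrower passages were being followed. The estimate will be imprecise (about ±0.69 SD at 16 per arm, ignoring clustering) and should be reported as an estimate, not a confirmatory test.

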1. *Who is responsible for identifying and recruiting individuals?*

🡪 Upon identification of potential subjects, our research team member (e.g., research assistant) will approach the interventionist emergency clinicians to see if his/her patient can be recruited for this study to confirm the inclusion/exclusion criteria.

1. *When and where individuals are recruited?*

🡪 Potential subjects will be recruited in the ED while receiving care.

🡪 After the intervention emergency clinician completes the TLT conversation, our research team member (e.g., research assistant) will approach the potential subjects or the surrogate for enrollment and completion of the patient-/surrogate-reported acceptability outcomes in the ED.

1. *How recruitment goals match the prevalence rates of the condition/disease being studied and the populations most impacted by the condition/disease being studied?*

🡪 We will recruit from all patients arriving in the ED, which will reflect the prevalence rates of seriously ill older adults in the ED.

1. *Methods to enhance enrollment of diverse individuals and under-represented populations*

🡪 We will cap enrollments of non-Hispanic Whites at 70% of the enrollment target and overenroll other under-represented minorities.

1. **SUBJECT ENROLLMENT**

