**Aim 2: Patient-reported Acceptability**

Pre-screening: We will identify potentially eligible patients using the ED track board in the EHR.

Consent Process:

1. Upon completion of TLT conversation by the interventionist emergency clinician (who also provides clinical care for the patient), our study team (e.g., research assistant, PI) will obtain verbal, informed consent from the patient or surrogate (if applicable) in the ED.
2. The capacity to consent the patient or surrogate is determined by the interventionist emergency clinician who conducted the TLT conversation.
3. **STUDY PROCEDURES**

**Intervention:** Clinician-led conversations about patient’s values and goals, potential benefits and risks of intensive care, and anticipated outcomes are standard of care in the ED. TLT is a multi-modal intervention that provides patient-centered structures to this standard of care. In this evaluation of TLT in the ED, the intervention components will include: 1) a structured conversation guide; 2) clinician training to use the guide; 3) electronic health records (EHR) template for documentation; and 4) standardized communication with the intensivist (**Fig 1**).

1. The TLT Conversation Guide: The structured conversation guide entails discussing patients’ values and goals, prognosis, and shared decision-making to use a trial of intensive care. Originally used in ICU settings,^21, 22^ we systematically refined the guide to be used in the ED incorporating inputs from patient advisors’ and emergency clinicians’ inputs (Appendix).
2. Clinician Training: Leveraging the study team’s expertise in serious illness communication training, the clinician training will include a one-hour didactic on research methodologies and serious illness communication skills, followed by a four-hour communication training with trained actors. Similar training has been described previously.^36-38^
3. EHR Documentation: An Epic template for documenting the TLT conversation findings has been developed (Appendix).
4. **
[figure not shown]
**Intensivist Communication: A standard template to communicate the TLT conversation findings to the intensivists has been developed (Appendix).

Control Group: Emergency clinicians assigned to the control group will not receive the TLT training/guide. Patients cared for by the control group emergency clinicians will receive usual care in the ED. No restrictions will be placed on serious illness conversations in the control group.

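### The secondary mixed model is set at baseline and one month, times at which no outcome in Table 2 supplies the data it needs, so it cannot be run as specified

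*Protocol*

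**What the plan says.** The Statistical Analysis section, under Aim 2, plans one longitudinal analysis: "We will conduct a secondary analysis using linear mixed models at baseline and one month to include all non-missing data". It does not name the outcome to be modelled.

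The measurement schedule is in Study Procedures, Table 2. Acceptability, Heard and Understood, and quality of communication are each timed "Immediately after the TLT conversation". Decisional regret is timed "After 24 hours, 48 hours, and 1 week", as is the inpatient documentation outcome under Aim 1. Clinical outcomes from the health record are timed "After discharge or upon patient death".

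Under Study Termination the protocol adds: "The follow-up assessments of the patients will terminate when/if the participants die or are discharged from the hospital".

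On the order of enrolment, the recruitment text in Subject Selection says: "After the intervention emergency clinician completes the TLT conversation, our research team member (e.g., research assistant) will approach the potential subjects or the surrogate". The consent process in Subject Enrollment likewise begins "Upon completion of TLT conversation by the interventionist emergency clinician".

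**The concern.** A mixed model at two time points needs at least one outcome observed at those times. The analysis sentence gives a pair of times that appears nowhere in the schedule, and the follow-up rule allows no assessment after discharge. Two parts of the same protocol therefore disagree about what data will exist.

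Two things are at stake. First, this is the only sentence on the Aim 2 outcomes that says anything about incomplete data, and as written it has nothing to work on. Second, decisional regret is the only patient-reported outcome measured more than once, yet the one longitudinal model in the plan is set at times that are not those of its schedule. Because assessments stop at discharge or death, regret at 1 week will be missing for anyone who has left hospital or died by then. That missingness is tied to the patient's course, and the analysis should make it visible.

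**Working it through.** No figure in the plan underlies this point, so there is nothing to reproduce. The check sets the model's two time points against every timing entry in Table 2, then against the enrolment sequence and the follow-up end rule.

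**Step 1. Schedule against the model's time points.**

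| Outcome (Table 2) | Scheduled time | Before the conversation? | One month? | Repeated? |
| --- | --- | --- | --- | --- |
| Conversation time (Aim 1) | At the conversation | No | No | No |
| Fidelity (Aim 1) | At the conversation | No | No | No |
| Clinician-reported feasibility (Aim 1) | Just after the conversation | No | No | No |
| Recruitment (Aim 1) | At enrolment | Not a repeated outcome (Step 2) | No | No |
| Clinician satisfaction (Aim 1) | Just after the conversation | No | No | No |
| Inpatient documentation (Aim 1) | 24 h, 48 h, 1 week | No | No | Yes |
| Acceptability (Aim 2) | Just after the conversation | No | No | No |
| Heard and Understood (Aim 2) | Just after the conversation | No | No | No |
| Quality of communication (Aim 2) | Just after the conversation | No | No | No |
| Decisional regret (Aim 2) | 24 h, 48 h, 1 week | No | No | Yes |
| Clinical outcomes (Aim 2) | After discharge or at death | No | No | No |

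Counts: 6 Aim 1 rows + 5 Aim 2 rows = 11 outcomes. Aim 2 instruments with a pre-conversation value: 0. Outcomes with a one-month value: 0. Outcomes with both: 0. Outcomes measured at more than one time: 2, of which 1 is patient-reported. The last fixed assessment is at 1 week.

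**Step 2. Could some entry serve as baseline?** The only row timed at enrolment is recruitment, defined as "The percent that agree to conduct TLT conversations". That is a participation percentage, not a first measurement of something measured again. The baseline characteristics mentioned in the analysis section are descriptive and are not a repeated outcome either. In the intervention arm a survey before the conversation is not possible under the stated sequence, since both approach and consent follow the conversation. Table 2 schedules no such survey in the control arm.

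**Step 3. A generous reading of baseline.** Suppose baseline means the survey in the emergency department just after the conversation. Three Aim 2 instruments are given then, and none is given again. Decisional regret is not given then. The count of outcomes with both times is still 0.

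**Step 4. Could some entry serve as one month?** Assessments end at death or discharge. A patient still in hospital at one month would remain within that rule, but nothing is scheduled for that day. The one-year period under Study Termination concerns following clinicians so that they accrue patients; it is not a patient assessment time.

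**The case against.** The strongest case on the other side is that little turns on this. The protocol calls the analysis secondary, in a pilot meant to show feasibility and acceptability. The primary feasibility outcome is the median conversation time. The outcomes named as primary for Aim 2 in different places, acceptability and Heard and Understood, are each measured once in the emergency department. None needs the mixed model. This stands, and it limits the weight of the point.

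It is also fair to say that model terms, the outcome to be modelled and the treatment of clinicians are often left to a statistical analysis plan, which may exist here unseen. Their absence from the protocol is not counted against it. That defence does not reach the time points, because an analysis plan cannot create assessments that the schedule omits.

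A reader might go further and infer several things that the document does not support:

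- *That no mixed model is possible.* One could be fitted to decisional regret; it would be a different analysis from the one written.
- *That most patients will be gone before one month, or that loss by 1 week is large.* The protocol gives no length-of-stay distribution. The hospital mortality of about 58% in Background and Significance covers the whole stay in an ICU quality-improvement study. It is not a 1-week figure and not from this population, so it cannot size the loss here.
- *That the replacement analysis will be chosen after the data are seen.* An analysis plan could restate the model beforehand.
- *That surveys after discharge or after a death are needed.* They would change study procedures and are not required to repair the sentence.

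**Conclusion.** The point holds as a contradiction within the protocol. The secondary linear mixed model is set at two times for which 0 of 11 outcomes supply a pair of values: none has a one-month assessment, and no Aim 2 instrument has a value from before the conversation. The follow-up end rule makes a one-month assessment impossible for anyone already discharged or dead. The analysis cannot be run as specified.

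The conclusion rests on taking Table 2 as the complete schedule and on the stated order of conversation, approach and consent. It does not depend on any assumption about mortality or length of stay. It should be corrected because the rule is wrong as written and the correction is cheap. It does not affect the primary outcomes, and nothing in the document supports treating it as a threat to the trial's main conclusions.

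**What to change.** Delete the reference to baseline and one month, and name the outcome and times. Suggested text: *Decisional regret at 24 hours, 48 hours and 1 week will be analysed with a linear mixed model including arm, time and arm-by-time, with a random intercept for patient and allowance for clustering by clinician where the number of patients per clinician supports it. The numbers alive and still in hospital at each time will be reported by arm.* The last sentence is needed because assessments stop at discharge or death.

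The clinician term is conditional because the sample-size text does not say who its 32 participants are. If they are patients, spread over the 40 clinicians in the design overview, there are 32 / 40 = 0.8 patients per clinician, and clinician and patient effects could hardly be separated. If they are clinicians, 16 per group with about 10 patients per interventionist gives 16 × 10 = 160 patients in the intervention arm, and the term is more plausible.

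This version costs a change of text only and adds no data collection. Its price is that it gives up any one-month comparison. If such a comparison is truly intended, the analysis sentence, Table 2 and the follow-up end rule must be reconciled by adding the assessments and changing the rule. That alters study procedures, so it is a larger amendment than the text change.
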